### Specific objectives

To identify the maximum tolerated dose (MTD) of intravenous sevuparin as an adjunctive therapy in children with severe malaria given as three infusions at 0, 8 and 16 hours using the Continual Reassessment Method (CRM) to adapt or inform subsequent doses for each child entering the trial, based on a toxicity event defined as any APTT >2.5 upper limit of normal (ULN) 1 hour after each dose, and updating the dose-toxicity model using the previous patients’ APTT results. The secondary objective will be to assess whether lactate clearance at 8 hours is a realistic and feasible primary endpoint for a subsequent Phase II trial.

## Methods

### Study sites

The study will be conducted on the high dependency ward in Kilifi County Hospital, Kilifi Kenya and the paediatric ward at Nchelenge Hospital, Luapula Province, Zambia

### Study design

A Phase I safety and dose finding trial

### Study populations

Twenty children hospitalised with severe malaria

### Inclusion criteria

1.   Aged between 3 months and 12 years admitted to the paediatric wards within the last 24h

2.   Current evidence of
*P. falciparum* malaria (slide positive)

3.   Clinical evidence of severe malaria: impaired consciousness: coma (inability to localize painful stimulus) or prostration (inability to sit unsupported for those above 6 months) or deep breathing

4.   Lactate > 2 mmol/L

5.   Guardian or parent willing and able to provide consent

### Exclusion criteria

1.   Clinical evidence or a history of a bleeding/coagulation disorder

2.   A comorbidity which clinician believes has a significant risk of poor outcome e.g., malignancy, end-stage renal failure, major cardiac condition

3.   Thrombocytopenia (platelet count <25 ×10
^9^/L).

## Sampling

### Sample size determination

This is a Phase I trial designed to obtain data on safety, dosing, feasibility, and lactate clearance of sevuparin given as an adjuvant therapy in severe malaria. We aim to study 20 children since this will allow sufficient data on safety to be generated across a range of doses to identify the maximum tolerated dose (MTD) from a more informed model relating dose to toxicity events (denoted the ‘dose- toxicity’ curve) than that available
*a priori* based on published data from adult studies. After each patient is enrolled, the dose-toxicity curve will be updated based on levels of APTT taken over three time points (1h post each infusion), defining a toxicity event as APTT >2.5xULN at any time point (grade 3 following the Common Toxicity Criteria (CTC)). This enables the MTD to be estimated more rapidly using the Continuous Reassessment Method (CRM)
^
59
^ once determined, subsequent participants will be allocated to this MTD to provide the most accurate estimate of future toxicity event rates until we reach the sample size of 20 children. However, the CRM method will continue to use information from all these children; for example, if a number of children receiving the originally identified MTD experience toxicity events, the dose would again be lowered, and future children would receive this lower dose.

**
*Sampling procedures and methods.*
** Children admitted to the paediatric wards of in Kilifi and Nchelenge Hospital children with suspected malaria and either coma or deep breathing (defining severe malaria for this Phase I study) will be screened by the paediatric triage/admission team for eligibility. Once eligibility is verified, the parents can be approached for consent and, if they agree to participate, they will receive their allocated treatment dosage. The blood tests taken at admission and during the trial include standard of care and research bloods (see
Table 2). Admission and serial assessment of full blood count, admission point of care clinical chemistry including PH, blood cultures and repeated assessment of malaria parasitaemia are part of the standard clinical tests. Additional to this will be serial assessment of lactate, measurements of coagulation (by iSTAT (Kaolin ACT) and laboratory-based APTT) and samples will be stored in Kilifi for future pharmacokinetic (PK) tests, plasma HRP2 tests and malaria parasites(research). The reliability of Point of care ACT measurements (using the iSTAT) have previously assessed against a laboratory gold standard and have shown that the coefficients of variation of POC ACT and whole blood were between 2% and 3.6%, indicating that POC assessments are reliable and able to support on-site decision-making for patients in acute and intensive care
^
60
^.

Management and outcome data will be collected (clinical parameters and recovery, developmental assessment, number of transfusions, use of drugs (specifically anticonvulsants, paracetamol, and antibiotics), date of discharge or in-hospital death. Contact and locator data will be recorded so that children can be followed at day 7 and day 28.

**
*Consent process.*
** Once eligibility has been confirmed, authorized trial staff will approach parents/guardians to invite their child to take part in the trial. An information sheet will be provided to the parent/guardian in their usual language. The sheet will be read aloud to those who are unable to read. The doctor/nurse will check that the information has been fully understood and parents/guardians will be encouraged to ask questions they may have about their child’s participation.

Where possible, prospective written informed consent will be sought from parents/guardians by asking them to sign the Consent Form. If parents/guardians are unable to sign, a thumbprint will be taken in lieu of a signature. A copy of the Consent Form will be given to the parent/guardian, the original placed in the patient’s medical notes, and a copy kept in the Investigator Site File.

If it is considered that the full consent process would significantly delay enrolment, and consequently be detrimental to the child’s health, then emergency verbal assent, used in previous trials
^
61
^, will be sought from parents/guardians by the admitting medical team. Following verbal assent, written informed consent will be sought from the parent as soon as possible once the child’s clinical condition has stabilized.

The participant information sheet, consent form and case report files can be found as
*Extended data*
^
62
^.

**
*Trial treatments.*
** We aim to study 20 children (See
Figure 1 Trial Flow). The trial will be open label with clinicians aware of study drug dosage. Laboratory staff performing APPT levels will be blind to drug dosage. All children will receive standard care including parenteral artesunate. Sevuparin will be given as three infusions at 0, 8 and 16 hours after enrolment. The initial participants (two ‘cohorts’ of 2 children each, i.e., 4 children in total) will receive a dose of 1.5 mg/kg/dose with the plan to escalate up to the next highest dose up to a maximum of 6.0 mg/kg/dose for subsequent children. In order to determine whether, and the rate of escalation, to move to a higher dosage for subsequent patients after the first 4 children we will use a design called the Continuous Reassessment Method (CRM). This starts with an
*a priori* dose-toxicity curve, reflecting the probability of experiencing a toxicity event (here APTT>2.5xULN 1h after any of the three doses) to the dose received. In this method of dose finding, the dose-toxicity curve is re-fitted to the data after each child is enrolled, based on their observed dose and whether they had a dose limiting toxicity event. After the first 4 children, each subsequent patient would be assigned the next highest dose, until the estimated risk of toxicity is just below or at the target toxicity level, designated as the maximum tolerated dose (MTD). The dose limiting toxicity (grade 3 APTT, >2.5xULN),
*a priori* dose-toxicity curve and chosen target toxicity rate (15%) used in this trial have been based upon data shared by the investigators from the adult sevuparin studies in Thailand [36]. In particular, almost all adults enrolled in this trial experienced grade 2 toxicity after one or more sevuparin doses, but APTT rapidly normalized, hence the choice of grade 3 toxicity to define the MTD in this dose-finding trial. APTT 24h post-enrolment is a key secondary safety endpoint to confirm rapid normalization.

**Figure 1. f1:**
[figure not shown]
Trial Flow

Any child with APTT>2.5xULN 1h after a dose of sevuparin will immediately discontinue trial treatment (and it would be counted as a toxicity event). They will continue to be followed according to the trial schedule (on-study, off-study-drug), to confirm resolution of APTT and to record clinical outcomes.

### Clinical assessments

Members of the clinical team and study team will all receive pre- and peri-trial training on the management of severe malaria. A manual of operations for the trial will be available for the study team, to anticipate and troubleshoot any potential issues. Vital signs will be monitored regularly (including temperature, heart rate, respiratory rate, blood pressure, oxygen saturation, conscious level). These will continue twice-daily after 24 hours until the child is discharged from HDU. All children will be managed on the HDU until conscious and able to take and retain oral fluids/food. During the period of sevuparin administration (0–24 hours) children in Kilifi, Kenya will have continuous electrocardiogram (ECG) monitoring for safety. However, it is notable that the trial in Thai adults showed no signs of QT prolongation
^
42
^. Once discharged from HDU children will be reviewed daily until discharge and followed up at day 7 and day 28. On admission and Day 28 children will be assessed by an adapted Kilifi Developmental Index to assess developmental status and clinically for neurodevelopmental sequelae (see
Table 2). Non-compliance is limited by the intervention being administered by clinical teams during admission. Any child who develops APTT>2.5xULN (grade 3 toxicity) will not receive further doses of sevuparin but will continue to be followed up. Children lost to follow-up before day 28 will be traced for vital status (permission requested within consent) using locator data and multiple contact phone numbers recorded before discharge.

**Table 2. T2:** Clinical management schedule.

	Assessment Time										
Procedure	Adm	1h	2h	4h	8h	9h	17h	24h	Bi daily to discharge	Day 7	Day 28
Clinical assessment	X	X	X	X	X			X	X	X	X
ECG continuous to 24 hours (Kilifi)	X							X			
APTT and coagulation tests (ACT) (1.7ml)	X	X 1 hr post dose				X 1 hr post dose	X 1 hr post dose	X			
Microperfusion ^ & ^	x					x	x				
Lactate (point of care)	X	X				X		X			
Standard clinical test non-research (FBC, POC chemisty Istat) *	X								X		X
Malaria slides	X					X		X	(36,48, 72 hrs)	X	X
Stored red cells & admission plasma **	X					X					X
PK sample		X				X					
Neuro-developmental assessment	X										X

^&^ Kilifi Site only

* Standard- non research clinical tests full blood count, clinical chemistry POC iSTAT (electrolytes, pH BUN) will be done at admission and at 24 hours and Day 7 (Full blood count only).

Other laboratory test: venous blood gases (including base excess) will be done at 0, 9 and 24 hours

Malaria slide and morphology will be done at 0, 9, 17, 24, 36, 48 hours (and 72 hours if in hospital); at follow up (Day 7 and 28)

**For quantitative plasma HRP2 assessment, biomarkers and parasite morphology (Kilifi site only)

### General clinical management

Children will initially receive parenteral antimalarial treatment (artesunate), followed by on day 3 (or when the child can safely take and retain oral feeds and fluids) an oral course of artemisinin combination therapy (ACT). All trial patients will receive intravenous antibiotics. Intravenous maintenance fluids will be given at a rate of 4ml/kg/hour until the child is able to drink and retain oral fluids. Antipyretics, anticonvulsants and treatment for hypoglycaemia and other treatments will be given as clinically required and will be administered according to nationally agreed protocols. Children with Hb <4 g/dl (or Hb <6 g/dl and respiratory distress) will be transfused with 20mls/kg of whole blood as soon as blood is available. In the absence of blood, standard care as per local treatment guidelines will be followed.

### Protocol treatment discontinuation

An individual patient may stop treatment early or be stopped early for any of the following reasons:

▪Unacceptable toxicity or adverse event▪Intercurrent illness that prevents further treatment▪Any change in the patient’s condition that justifies the discontinuation of treatment in the clinician’s opinion▪Withdrawal of consent for treatment by the patient or parent.

Participation in the trial is entirely voluntary, and parents, carers or older children may choose to discontinue the trial treatment at any time without penalty or loss of benefits to which they are otherwise entitled. Although not required to give a reason for discontinuing their trial treatment, a reasonable effort should be made to establish this reason while fully respecting the patient's rights.

Patients should remain in the trial for the purpose of follow-up wherever possible (unless the patient withdraws their consent for follow-up). If a patient withdraws from the trial, the medical data collected during their previous consented participation in the trial will be kept and used in analysis. This will also apply to parents/carers who withdraw from the trial after assent, that have not completed the deferred consent process. Consent for future use of stored samples already collected can be refused when leaving the trial early (but this should be discouraged and should follow a discussion). If consent for future use of stored samples already collected is refused, then all such samples will be destroyed.

### Trial products, storage and accountability

The drug product, sevuparin 150 mg/mL solution for intravenous (IV) infusion, is formulated in a 0.015M phosphate buffer at a pH of 7.0. It requires storage in a refrigerator at 2–8° and to be protected from light. The non-preserved sterile solution needs to be dispensed (5.4 mL) in a glass vial sealed with a rubber stopper and covered with a tear-off aluminum cap. The solution for administration will be prepared in a syringe and will be kept refrigerated and used within 24 hours. One vial will only be used for one subject. The drug product is produced in compliance with current Good Manufacturing Practice (GMP). The same material and compositions has been used in a clinical trial in children with sickle cell disease
^
43
^. from the product has been donated by MODUS Therapeutics, Sweden for use in this trial.

## Sub studies

### Assessments of the pharmacokinetics of Sevuparin

An aliquot of plasma from the samples taken during the trial will allow pharmacokinetic- pharmacodynamic (PKPD) modelling of the relationships between drug levels and longitudinal APTT and plasma lactate levels. The evaluation of the PK data will focus on the association between the sparsely sampled sevuparin concentrations and the APTT levels, plasma lactate levels and renal function. These assays will be contracted to Accelera (Nerviano (MI), Italy) since they have validated methodology for Sevuparin measurement and the data sent to MORU, Bangkok who will undertake tbe PK modelling at the end of the clinical study.

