**Methods:**

A Phase I trial designed to provide data on safety, dosing, feasibility of sevuparin as an adjuvant therapy in Kenya and Zambian children with severe malaria complicated by lactic acidosis (> 2mmol/l). Three intravenous doses will be given at admission (0 hours), 8 and 16 hours. APPT will be measured 1 hour after each dose (to assess maximum toxicity). Studying 20 children will allow sufficient data on safety to be generated across a range of doses to identify the maximum tolerated dose (MTD) using the Continual Reassessment Method, which adapts or informs subsequent doses for each child based on the data from previously enrolled children. The MTD will be identified based on the dose-toxicity model updated by each previous patient’s APTT results using standard methods.

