In the Phase I dose escalation trial, sevuparin was found to be safe and well-tolerated with minimal effects on APTT at doses of 1.5 mg/kg and 3mg/kg every six hours but a dose of 6.0 mg/kg led to higher APTT values. The Data Monitoring Committee (DMC) therefore recommended that the study should continue to the Phase II with a dose of 3.0 mg/kg sevuparin every 6h, given the potentially increased risk of adverse events at higher doses
^
42
^.

In the Phase II trial, sevuparin was administered as an intravenous infusion over 5 minutes in addition to standard care i.e., a fixed dose combination of 1000 mg atovaquone and 400 mg proguanil once daily for three days, in subjects with uncomplicated
*P. falciparum* malaria (experimental arm), as compared to atovaquone/proguanil treatment alone (control). There were minimal and non-clinically relevant changes in anti-Xa- and prothrombin-times, and the international normalized ratios associated to the sevuparin dose. Increases in APTT were dose-dependent and appeared to follow the time-concentration curve for each sevuparin infusion. The 6-hour interval between the infusions allowed for nearly full reversibility of APTT levels after each dose, and no accumulative effects were seen over the course of the 12 consecutive infusions. Thrombocytopenia occurred in one subject but was noted to be present before the initiation of sevuparin treatment. There was no incident of bleeding in any of the participants nor were there any other serious adverse events or adverse events
^
42
^.

Sevuparin was therefore judged to be safe and well tolerated in adults with mild malaria and was found to safe with minimal side effects in other clinical trials
^
43
^. It led to a reduction in numbers of ring-stage infected erythrocytes after a single sevuparin infusion and resulted in a transient appearance of mature parasite infected erythrocytes (schizonts appearing in the circulation, indicating these had been released after desequestration). These both occurred within one hour after the first sevuparin injection. Thus, these studies indicate that a novel new drug candidate for adjunctive treatment of severe malaria had been identified that blocks merozoite invasion and transiently de-sequesters infected erythrocytes in humans with uncomplicated
*P. falciparum* malaria.

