### Safety endpoints

APTT 24h post enrolment (absolute level and grade)

Development of abnormalities of coagulation indices (prothrombin) (Grade 2 and above)

Neurological sequelae through day 28

Mortality through day 28

Serious adverse events through day 28

Grade 3/4 adverse events through day 28

APTT 24h post enrolment will be used as an assessment of normalization 8h after the final sevuparin dose. Both absolute levels and grade will be considered.

De-novo evidence of neurological sequelae will be ascertained using a modified Kilifi Developmental Index
^
63
^ assessed at admission (to identify pre-existing conditions) and follow up (which we have adapted to use for the other trials.

Serious adverse events will use the standardized definitions (see section 11 below). SAEs will be independently reviewed in real-time by the DMC. Adverse events will be graded following the Common Toxicity Criteria v5.0: (
https://ctep.cancer.gov/protocoldevelopment/electronic_applications/docs/CTCAE_v5_Quick_Refe rence_5x7.pdf).

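### Both scheduled PK samples fall 1 h after an infusion, so the PKPD modelling has little information on elimination or its relation to renal function, and no concentration to pair with the 24 h APTT

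*Protocol article*

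**What the plan says.** On dosing, the Trial treatments paragraph states: "Sevuparin will be given as three infusions at 0, 8 and 16 hours after enrolment".

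Table 2 (Clinical assessments) has the time columns "Procedure Adm 1h 2h 4h 8h 9h 17h 24h", followed by later visits. The PK row is marked under 1 h and 9 h only. The APTT row is marked at admission, 1 h, 9 h, 17 h and 24 h, and the 1, 9 and 17 h entries are labelled as one hour after a dose. Point-of-care lactate is marked at admission, 1, 9 and 24 h. The footnote gives BUN at admission and 24 h.

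On the aim, the section on the pharmacokinetics of sevuparin says: "An aliquot of plasma from the samples taken during the trial will allow" pharmacokinetic-pharmacodynamic "modelling of the relationships between drug levels and longitudinal APTT and plasma lactate levels". The evaluation is to focus on the "association between the sparsely sampled sevuparin concentrations and the APTT levels, plasma lactate levels and renal function". That section gives no sampling times.

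On the 24 h reading, the Safety endpoints section says: "APTT 24h post enrolment will be used as an assessment of normalization 8h after the final sevuparin dose". Trial treatments names it a key secondary safety endpoint.

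**The concern.** The aim and the sampling times do not fit together well. Modelling drug level against APTT over time, and relating exposure to renal function, needs information on how fast the drug leaves. Two concentrations taken at the same time after dosing say a good deal about the level at that time and little about its decline. The one APTT value that is off peak in a fully dosed child, at 24 h, has no concentration marked beside it.

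At stake is how much the sub-study can tell Phase II about exposure between doses and in children with impaired renal function. Sampling times are settled at the bedside, and no later analysis plan can recover concentrations that were not kept and assayed.

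**Working it through.** The plan states no PK figure (no half-life, precision target or PK sample size), so there is no figure of its own to reproduce. The check rebuilds the timing and then asks how much the scheduled samples say about elimination.

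**Step 1: time since last infusion.** Infusions are at 0, 8 and 16 h.
- PK: 1 − 0 = 1 h and 9 − 8 = 1 h.
- APTT: baseline, then 1 − 0 = 1 h, 9 − 8 = 1 h, 17 − 16 = 1 h and 24 − 16 = 8 h.

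**Step 2: accumulation.** For a one-compartment model with short infusions treated as bolus doses and half-life h, C(9)/C(1) = 1 + 2^(−8/h).
- h = 1: 1 + 2^(−8) = 1.004
- h = 2: 1 + 2^(−4) = 1.063
- h = 3: 1 + 2^(−2.67) = 1.158

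The half-lives are assumptions.

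**Step 3: what an off-peak sample would show.** Ignoring carry-over, C(24)/C(17) = 2^(−7/h), which is 0.8%, 8.8% and 19.8% for h = 1, 2 and 3. That is a span of about 25-fold (19.8/0.8), against 1.004 to 1.158 in step 2.

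**Step 4: precision with 20 children.** This uses the linearised population information for log k (elimination rate) and log V (volume). Assumptions are 30% between-child variability in k and in V, and 20% residual error. The variance ratio is the share of the prior variance of an individual child's k that remains after seeing that child's samples. A value near 1 means almost nothing was learned about that child.

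| Half-life (h) | C(9)/C(1) | SE log k, 1 and 9 h | Variance ratio | SE log k, 24 h added | Variance ratio |
|---|---|---|---|---|---|
| 0.5 | 1.000 | 374 | 0.39 | 0.07 | 0.01 |
| 1 | 1.004 | 2.93 | 0.71 | 0.07 | 0.02 |
| 1.5 | 1.025 | 0.71 | 0.82 | 0.07 | 0.05 |
| 2 | 1.063 | 0.39 | 0.85 | 0.07 | 0.08 |
| 3 | 1.158 | 0.26 | 0.85 | 0.07 | 0.15 |
| 4 | 1.250 | 0.24 | 0.86 | 0.08 | 0.20 |
| 6 | 1.397 | 0.25 | 0.89 | 0.08 | 0.31 |

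The 0.39 at 0.5 h arises only because V is assumed known to within 30%. The columns with 24 h added assume that the 24 h value is above the assay limit.

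On the ratio scale, an SE of 0.39 gives a 95% interval of exp(1.96 × 0.39), about 2.1-fold either way. An SE of 0.26 gives about 1.7-fold, and 0.07 about 1.15-fold.

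**Step 5: adding 17 h instead of 24 h.** This is a third sample 1 h after dosing. The SE of log k becomes 2.53, 0.32 and 0.20 at 1, 2 and 3 h, so it adds little by itself.

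**Step 6: children stopped early.** A child stopped after a toxicity event at the first dose stays on the schedule, so that child's 9 h sample is off peak. At the 15% target rate about 20 × 0.15 = 3 children would have an event, and only those with the event after dose 1 would contribute. They would also be selected for high APTT.

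**The case against.** A reader might infer that the model cannot estimate elimination, its renal dependence or the APTT time course at all. The documents do not support that, for these reasons.

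- Elimination is formally identifiable through accumulation and roughly estimable at half-lives of 3 h or more (SE about 0.25). If children with renal impairment clear the drug slowly, the 9 h to 1 h ratio would begin to show it.
- APTT decline is itself observed, at baseline and 8 h after the third infusion. What is missing is the paired concentration.
- The stated focus is association using openly sparse data; half-life and clearance are not named. The relation of 1 h concentration to same-time APTT and lactate, and to BUN, can be examined as scheduled.
- The adult evidence, "The 6-hour interval between the infusions allowed for nearly full reversibility of APTT levels after each dose, and no accumulative effects were seen", concerns APTT in adults with uncomplicated malaria. The SEVUPARIN section adds that APTT appeared to follow the concentration curve, which makes little carry-over plausible, but it reports no drug levels and does not show the same for severely ill children.
- The CRM curve already relates toxicity to dose, so the PKPD model is not the only route from these data to Phase II.
- The Abstract says "APPT will be measured 1 hour after each dose (to assess maximum toxicity". It is tempting to add that the schedule cannot test whether 1 h is the peak. A 17 h or 24 h concentration would not test that either, so it is not part of this point.

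All of these stand and limit the point.

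Two further objections are weaker. The sub-study text takes aliquots from trial samples without limiting the times, so 17 h and 24 h plasma may be intended. If so, Table 2 should mark it. It is also true that a condensed article leaves detail to the full protocol, but this one prints both the sampling times and the aim, and these are what do not match.

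**Conclusion.** The point holds in limited form. Table 2 schedules both PK samples 1 h after an infusion. For a fully dosed child this leaves little information on elimination if the half-life is about 2 h or less (SE of log k 0.39 at 2 h and 2.9 at 1 h), and rough information above that. From 1 h upwards, an individual child's elimination rate keeps 71% to 89% of its prior variance, so a relation between clearance and renal function is not usefully estimable. The 24 h APTT has no marked concentration.

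These sizes rest on a one-compartment model and on assumed half-lives and variabilities, none of which the documents give. The timing itself needs no assumption. The consequence is confined to the sub-study: no primary, secondary or safety endpoint is a PK parameter, and choice of the MTD does not use concentrations. It is a cheap improvement worth making, not a threat to the trial.

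**What to change.** In Table 2, mark a PK aliquot at the 24 h APTT draw, which is 8 h after the third infusion. Under the assumptions above, and if values are above the assay limit, this brings the SE of log k to about 0.07 to 0.08 and the individual variance ratio to 0.01 to 0.31. Optionally mark 17 h as well, as the 1 h value within the same dosing interval. Keep the 9 h sample: it pairs with the 9 h APTT, and Table 2 has no APTT at 8 h. State the same times in the pharmacokinetics section so that the text and the table agree.

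If no further aliquot can be assayed, limit the stated aim to the relation of the 1 h concentration to APTT, lactate and renal function.

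The cost is one assay per child (two with 17 h) on blood already drawn. With a short half-life some 24 h values may fall below the assay limit, so the modelling should treat them as censored rather than drop them.
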